
In summary, while Anti-Xa measurement is considered the gold standard for monitoring heparins, its predictive value for adequate prophylaxis or therapy in critically ill patients is uncertain. VET and TGA offer broader insights into haemostasis but yield inconsistent results, particularly at low LMWH doses, and remain poorly standardized. Major gaps therefore persist: fixed dosing yields unpredictable Anti-Xa levels; validated therapeutic and prophylactic targets are lacking; the relationship between Anti-Xa and global haemostatic function is unresolved; and the interplay among dosing, Anti-Xa activity, VET, TGA, and patient-specific factors has not been systematically evaluated.

The present protocol addresses these gaps through a prospective observational study in critically ill adults receiving UFH or LMWH. By concurrently measuring Anti-Xa, viscoelastic variables, thrombin generation, and standard laboratory tests, this study aims to determine whether the VET can serve as a reliable surrogate for Anti-Xa monitoring to obtain a broader view of the coagulation system in critically ill patients.

Because Anti-Xa quantifies UFH and LMWH activity in plasma whereas VET reflects whole-blood clot formation influenced by both anticoagulant exposure and the patient’s haemostatic substrate, a strong correlation is not guaranteed in critical illness. The primary objective is therefore pragmatic: to determine whether CT in RVV assay shows a sufficiently stable, monotonic relationship with Anti-Xa to support bedside interpretation as a rapid surrogate for Anti-Xa activity, and to define possible conditions under which this relationship worsens. A stable correlation would support CT-guided interpretation when Anti-Xa results are delayed or logistically constrained; conversely, weak or heterogeneous correlation would question whether VET-based monitoring offers advantages and underscore the need for complementary testing. Associations with clinical outcomes are collected as exploratory signals; the study is not powered to rank assays by clinical endpoints.

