The Anti-Xa level at the time of sampling reflects the plasma concentration of the anticoagulant and allows consideration of individual variations in drug absorption and elimination. Interpretation of Anti-Xa activity will account for concomitant antithrombin levels, as assay results depend on endogenous antithrombin when no supplementation is included in the reagent, and may be influenced by reagent composition and acute-phase proteins, particularly in patients receiving UFH. For example, high catecholamine requirements or microcirculatory disturbances, such as those occurring during sepsis, may impair the absorption of subcutaneously administered drugs, leading to subtherapeutic plasma levels and necessitating dose escalation. Conversely, reduced drug elimination, such as in renal failure, may cause accumulation and supratherapeutic levels. To account for the specific haemostatic alterations seen in sepsis, sepsis-specific scores will be recorded. Additional laboratory analyses will include prothrombin fragments 1 + 2 (PF1 + 2), thrombin generation assay (TGA), plasmin-antiplasmin complexes (PAP), plasminogen activator inhibitor (PAI), tissue factor pathway inhibitor (TFPI), and thrombin-antithrombin complexes (TAT) to detect hypercoagulable states and/or impaired fibrinolytic activity. SLTs will also be performed to improve comparability among the heterogenous ICU population and to enable subgroup analyses. The anticoagulants of interest are LMWH and UFH. VET testing will be performed using the RVV-test for LMWH and UFH. Both groups will additionally undergo measurements via extrinsic (EX) and Russell viper venom with heparinase (RVH) tests. Measurements will be performed in patients with prophylactic, intermediate, and therapeutic anticoagulation targets, allowing comparisons of the correlation and adjustability of individualized anticoagulation across different degrees of anticoagulation intensity. Figure 1 provides an overview of the temporal sequence of measurements and planned analyses in the study.

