### Viscoelastic testing

2.7

Viscoelastic testing will be performed immediately on the ICU using the ClotPro® device. Testing will follow manufacturer-specific standard operating procedures. After electronic patient identification entry, the corresponding test channel and cartridge will be selected. Test-specific pipette tips will be scanned, and citrated whole blood will be transferred into the test cup, gently mixed, and the measurement initiated.

The following assays will be performed according to anticoagulant type:

LMWH / UFH: EX-, RVV-, RVH-, ECA-test.UFH: additional IN/HI-test.

Recorded parameters include CT, CFT, A5, A10, MCF, lysis time (LT), maximum lysis (ML), and alpha angle. Time from sampling to test initiation will be documented. After test completion, measurement channels will be prepared according to hygiene standards. Residual blood will be discarded in designated biohazard containers. The POC devices used in this study, which are operated outside the central laboratory, undergo weekly quality control in accordance with the manufacturer’s specifications.

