#### Primary analysis

2.13.1

The primary outcome, defined as the correlation between Anti-Xa activity (UFH/LMWH) and CT in the RVV-assay. Because two measurements per patient are planned, the primary inferential analysis will be conducted using a linear mixed-effects model including:

A random intercept for patientA fixed effect for anticoagulant type (UFH vs. LMWH)

This approach accounts for intra-individual correlation and avoids inflation of type I error due to non-independence of repeated observations. Results will be reported as regression slope estimates (per 0.1 IU/mL increase in Anti-Xa activity) with 95% confidence intervals. For descriptive comparability with previous literature, Spearman rank correlation coefficients with bootstrap-derived 95% confidence intervals will additionally be reported:

For the overall cohortStratified by anticoagulant type

Passing–Bablok regression will be applied as a robust method-comparison technique to assess proportional and systematic bias between CT-RVV and Anti-Xa activity (36). Proportional bias will be considered absent if the 95% confidence interval (CI) of the slope includes 1.0, and constant bias absent if the 95% CI of the intercept includes 0.

These criteria are used for methodological characterization rather than to demonstrate assay equivalence. The primary objective is not interchangeability but to determine whether CT-RVV exhibits a stable monotonic relationship with Anti-Xa activity under ICU conditions.

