#### Pre-specified effect modification analyses

2.13.2

To explicitly address biological heterogeneity in critically ill patients, potential effect modifiers will be analysed within the mixed-effects framework using interaction terms.

Pre-specified modifiers include:

Sepsis statusAntithrombin concentrationRenal function (creatinine, estimated GFR)Inflammatory markers (CRP, fibrinogen, albumin)

Sepsis status will be analysed as an effect modifier rather than as a separately powered subgroup.

These analyses aim to identify conditions under which CT-RVV and Anti-Xa activity diverge.

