#### Secondary analysis

2.13.3

To limit multiplicity and reduce type I error inflation, secondary analyses are structured into predefined parameter families.

Additional VET Parameters: CFT, A5, A10, MCF, *α*-angle, lysis time, maximum lysisDescriptive Spearman correlations with Anti-XaMixed-effects regression models to explore surrogate potentialStandard Laboratory Assays: INR, aPTT, fibrinogen, platelet count, antithrombin, bilirubin, triglycerides, albuminPartial correlationsMultivariable mixed-effects regressionStandardized *β*-coefficients with 95% confidence intervalsChange in explained variance (Δ*R*^2^)Advanced Haemostatic Markers: FVIII, FXIII, thrombin generation parameters, PAP, PAI-1, TFPI, TATDescriptive correlation analysesComparative interpretation of effect sizes

False discovery rate correction using the Benjamini–Hochberg procedure will be applied within each predefined parameter family.

All baseline characteristics will be summarized descriptively. Categorical variables are reported as counts and percentages. Continuous variables will be summarized as mean ± SD if normally distributed or as median (IQR) if non-normally distributed. Normality will be assessed using the Shapiro–Wilk test.

All analyses will be conducted using SPSS® (version 27, IBM Corp., Armonk, NY, USA) and RStudio (Posit Software, PBC, Boston, USA, version 2025.05.0 + 496). A two-sided *p*-value <0.05 will be considered statistically significant.

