
Sepsis, multi-organ failure, and endothelial dysfunction alter pharmacokinetics and pharmacodynamics, complicating both drug absorption and elimination. Consequently, Anti-Xa monitoring provides only a concentration-based readout and does not reflect the complex interplay between the procoagulant and anticoagulant pathways. In particular, it neglects the influence of elevated fibrinogen levels due to inflammation, increased platelet activation, and impaired fibrinolytic activity. Similarly, standard laboratory tests such as aPTT and INR are confounded by acute-phase reactants and inflammatory mediators. Additionally, Anti-Xa activity reflects heparin-dependent inhibition of a fixed amount of exogenous factor Xa and is therefore largely independent of endogenous factor X levels. In contrast, CT-RVV in whole blood may be influenced by variations in coagulation factor concentrations, including factors V and X. Such variability is considered part of the biological context of critical illness and is not treated as methodological noise but as a potential modifier of assay concordance. As a result, neither Anti-Xa nor conventional coagulation tests adequately capture the dynamic risk of bleeding and thrombosis in critically ill patients.

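### CT-RVH is measured on every sample but named in no described analysis, and the modifier list has no direct measure of heparin-independent variation in CT-RVV

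*Protocol article*

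**What the plan says.** Collection. Section 2.2 (Trial design) states: "Both groups will additionally undergo measurements via extrinsic (EX) and Russell viper venom with heparinase (RVH) tests". Section 2.7 (Viscoelastic testing) gives the panel common to both drugs as "LMWH / UFH: EX-, RVV-, RVH-, ECA-test". The Figure 1 legend adds that all assays come from the same sampling time point, so each CT-RVV has a paired CT-RVH.

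Analysis. The primary model in 2.13.1 has Anti-Xa, anticoagulant type and a patient random intercept. It reports "regression slope estimates (per 0.1 IU/mL increase in Anti-Xa activity) with 95% confidence intervals". The list in 2.13.2 that opens with "Pre-specified modifiers include" contains sepsis, antithrombin, renal function and three inflammatory markers (CRP, fibrinogen, albumin). The viscoelastic family in 2.13.3 begins "Additional VET Parameters: CFT, A5, A10, MCF" and goes on to alpha angle and lysis variables. It names no assay and does not list CT.

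Rationale. The Introduction gives the aim as "to determine whether CT in RVV assay shows a sufficiently stable, monotonic relationship with Anti-Xa to support bedside interpretation as a rapid surrogate", and adds that the study will define conditions under which the relationship worsens. The Discussion says that "CT-RVV in whole blood may be influenced by variations in coagulation factor concentrations, including factors V and X", whereas Anti-Xa is largely independent of endogenous factor X. It then says: "Such variability is considered part of the biological context of critical illness and is not treated as methodological noise but as a potential modifier".

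**The concern.** The rationale and the analysis list do not meet. The Discussion assigns heparin-independent variation in CT-RVV the role of a modifier. Section 2.13.2 exists to find conditions under which CT-RVV and Anti-Xa diverge, but none of its variables measures that variation directly. Factors V and X are not among the measured variables in 2.6 or Table 1. If heparinase neutralises the heparin in the sample, the RVH test is the same test without the drug effect. CT-RVH is then the most direct measure collected of the part of CT-RVV that Anti-Xa cannot see.

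What is at stake is how a weak result would be read. The Discussion itself cites a larger critically ill cohort in which CT-RVV correlated only weakly to moderately with Anti-Xa, so a weak result is realistic. It could mean that the RVV test responds poorly to heparin. It could also mean that the test responds well but that differences in baseline clotting hide the response. The two explanations lead to different conclusions about bedside use. Choosing CT-RVH as an explanatory variable after seeing the data would be the data-driven inference that 2.13 sets out to avoid.

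**Working it through.** **No plan figure to reproduce.** The documents give no variance for CT-RVV or CT-RVH and no correlation involving CT-RVH. The sample size figures in 2.12 do not bear on this point.

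**Step 1: where RVH appears.**

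| Place | RVH or CT-RVH named? |
|---|---|
| Abstract, 2.2, Figure 1 legend, 2.7, Table 1 (collection) | Yes |
| 2.10 outcomes | No |
| 2.13.1 primary model | No |
| 2.13.2 modifiers | No |
| 2.13.3 parameter families | No |
| 2.16 additional analyses | No; refers to VET parameters in general |

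**Step 2: what the covariate could remove.** Let p be the partial correlation of CT-RVH with CT-RVV given Anti-Xa. This is an assumption, with range 0.3 to 0.7. The remaining share of residual variance is 1 − p².

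- p = 0.3: 1 − 0.09 = 0.91, a fall of 9%
- p = 0.5: 1 − 0.25 = 0.75, a fall of 25%
- p = 0.7: 1 − 0.49 = 0.51, a fall of 49%

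**Step 3: effect on an illustrative correlation.** Take r = 0.40 (assumed) and CT-RVH uncorrelated with Anti-Xa. With b² = r²/(1 − r²) = 0.16/0.84 = 0.190, the adjusted correlation is √[b²/(b² + 1 − p²)].

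- p = 0.3: √(0.190/1.100) = 0.42
- p = 0.5: √(0.190/0.940) = 0.45
- p = 0.7: √(0.190/0.700) = 0.52

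Steps 2 and 3 leave out the random intercept and the drug-type term, which already take up part of the between-patient variance.

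**Step 4: the planned model structure.** A simulation used 66 patients with two samples each, 80 runs per setting and a true slope of 1. It assumed heparin-independent CT variance of 0.5 to 2 times the heparin-driven variance, and an intraclass correlation of 0.7 for CT-RVH. Some fits gave convergence warnings, so the results are approximate.

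| Correlation of CT-RVH with Anti-Xa | Without CT-RVH | With CT-RVH |
|---|---|---|
| 0 | slope 0.98 to 1.02, SE 0.100 to 0.136 | SE 0.081 to 0.083 |
| −0.3 | slope 0.65 to 0.82 | slope 0.98 to 1.01 |
| +0.3 | slope 1.18 to 1.33 | slope 0.98 to 1.01 |

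With no correlation, omitting CT-RVH costs precision only. With a correlation, the unadjusted slope differs from the heparin-only slope, and the random intercept does not prevent this. The documents do not say which row applies.

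**Step 5: a labelling conflict.** Section 2.2 defines RVH as the RVV test with heparinase. The abbreviation list under Table 1 has the word high where heparinase would stand. The argument here uses the 2.2 definition.

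**The case against.** The strongest reply is that the primary analysis asks the right question. The aim is whether CT-RVV as read at the bedside tracks Anti-Xa. For that aim, scatter from coagulation factors is part of the answer, and the Discussion keeps it in deliberately. This stands. A reader might infer that the primary slope is confounded or defective. The documents do not support that: it would follow only if the slope were read as the isolated effect of heparin on CT, which the protocol does not claim.

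Second, a condensed article may leave a supporting model to the analysis plan, which is not shown, and general references to VET parameters could cover some RVH variables. This stands in part. It is too strong to say that RVH enters no analysis; what can be said is that CT-RVH is named in none of those described. But the article does set out its modifiers, and that list does not match its own rationale.

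Third, discordance is examined through the listed modifiers, through standard laboratory assays with partial correlations and change in explained variance, and through biomarkers included to characterise discordant profiles. This also stands in part, so it would be wrong to say that the plan cannot address the question. These are, however, proxies for what CT-RVH is designed to show.

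Fourth, CT-RVH isolates the heparin-independent part only if neutralisation is complete, which the documents do not state. This is a fair caution for interpretation. It is not a reason to leave the measurement unused.

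**Conclusion.** The point holds as a gap between the stated rationale and the named analyses, and it is a cheap improvement. It is not an error in the primary model. As described, a weak CT-RVV/Anti-Xa association could be attributed only indirectly to poor heparin sensitivity or to baseline clotting differences.

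The size cannot be derived from the documents. The 9% to 49% fall in residual variance rests wholly on the assumed partial correlations. A reader might turn it into patient numbers (66/0.91 ≈ 73 up to 66/0.51 ≈ 129), but that would not describe the planned mixed model, for the reason given after Step 3. The slope shifts in Step 4 likewise depend on an assumed correlation between CT-RVH and Anti-Xa.

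**What to change.** 1. Keep the unadjusted CT-RVV/Anti-Xa mixed model as primary.
2. Add to 2.13.1 one pre-specified supporting mixed model with CT-RVH from the same sample as covariate, on the log scale if CT is log-transformed. Using log(CT-RVV/CT-RVH) as the outcome is a separate alternative. It forces the coefficient of log CT-RVH to 1, whereas the covariate model estimates it, so the two can give different slopes.
3. Add Anti-Xa × CT-RVH to the modifiers in 2.13.2, labelled exploratory.
4. Reconcile the two expansions of RVH in 2.2 and under Table 1.

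The cost is one more estimate to report and one more exploratory interaction, on data already collected. Because 2.15 rules out imputation, samples without a valid RVH result drop out of the supporting model. The unadjusted slope should therefore also be shown on that same subset, so that the two can be compared.

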## Introduction

1

Thromboembolic events remain a major cause of morbidity and mortality in critically ill patients (1–4). Despite pharmacological prophylaxis, 5–15% of patients in intensive care units (ICUs) develop deep vein thrombosis (DVT), which is associated with prolonged mechanical ventilation and extended ICU and hospital stays (5–8). Low-molecular-weight heparins (LMWHs) are preferred over unfractionated heparin (UFH) because of their greater antithrombotic efficacy and lower complication rates (9, 10). Optimal anticoagulation requires the risk of thrombosis and bleeding to be balanced. Although LMWHs are often assumed to have predictable pharmacokinetics permitting fixed dosing without monitoring, this assumption does not apply in critical illness. The reported therapeutic failure rates range from 12 to 20%, underscoring the potential value of individualized anticoagulation guided by therapeutic drug monitoring (TDM) (2, 4, 11). Prospective studies have demonstrated wide interindividual variability in Anti-Xa activity despite standardized dosing, largely due to sepsis, multiorgan failure, endothelial dysfunction, and fluid shifts (12, 13). A systematic review of 18 studies including 1,644 ICU patients reported low peak Anti-Xa levels ranging from 0.1 to 0.35 IU/mL, although no consistent association with bleeding was revealed (14). These results indicate that fixed dosing may result in both under- and overtreatment (15–17). Anti-Xa monitoring is already recommended for specific comorbidities, such as obesity and renal impairment (1, 10), but its routine use in ICUs is limited by logistical barriers and turnaround times. Moreover, while Anti-Xa accurately reflects drug concentration, it does not capture the global haemostatic status, which may be profoundly altered in critical illness (18). Standard laboratory tests (SLTs), such as aPTT, fibrinogen, and INR, correlate poorly with anticoagulant effects in ICU patients and are influenced by factors unrelated to heparin activity, such as elevated factor VIII, resulting in misleading results (18, 19). Anti-Xa measurement directly quantifies the pharmacodynamic effects of UFH and LMWH and is considered the reference standard (1, 10, 19), but it remains an incomplete surrogate for haemostatic balance. Viscoelastic testing (VET) offers functional, point-of-care (POC) assessment of coagulation, integrating plasmatic and cellular components in real time. Devices such as TEG6s®, ROTEM®, and ClotPro® measure clot initiation, propagation, firmness, and fibrinolysis in whole blood (20, 21). Several studies have attempted to correlate VET variables with Anti-Xa activity, with mixed results. *In vitro* experiments using TEG6s® demonstrated strong correlations between clotting time (CT) and heparin concentration, with classification accuracies >90% for UFH and >78% for LMWH (22). Healthy volunteer studies have shown a strong correlation between TEG® reaction time and Anti-Xa (*r* = 0.82) and improved prediction using composite variables (23). Modified ROTEM® assays demonstrated near-linear relationships between Anti-Xa and CT (*r* ≈ 0.93) in spiking experiments (24). However, the clinical data are inconsistent: some studies reported no correlation between TEG® reaction time and Anti-Xa beyond single peak levels after LMWH dosing (25); others reported that conventional ROTEM® variables failed to detect prophylactic LMWH effects (26), whereas modified ClotPro® assays showed improved sensitivity (27). Overall, the sensitivity of LMWH to VET appears to be highly context- and assay-dependent (28). Thrombin-generation assays (TGAs) provide a complementary global evaluation by quantifying thrombin kinetics and overall generation. Although their use is hampered by limited standardization, automated TGA platforms have demonstrated good correlation with Anti-Xa at therapeutic LMWH doses and may detect reduced thrombin generation in suspected heparin resistance (29). In critically ill children, the endogenous thrombin potential correlated moderately with the TEG® kinetic time and more strongly with Anti-Xa during extracorporeal support (30). These findings emphasize that Anti-Xa, VET, and TGA capture distinct but overlapping aspects of haemostasis: Anti-Xa reflects drug concentration, whereas VET and TGA integrate functional contributions from coagulation factors, fibrinogen, and platelets (31).

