1) Variable: Additional VET variables (CFT, A5, A10, MCF, *α*-angle, lysis time, and lysis index).Metric: Spearman correlations with Anti-Xa and TGA variables; multivariable mixed-effects regression to account for repeated measures.Aggregation: Correlation coefficients (*r*) with 95% CI; regression *β* with 95% CI.Time point: As in primary outcome.Clinical relevance: Explores whether extended VET variables provide complementary or superior information to CT for characterizing anticoagulant effect.2) Variable: Advanced haemostatic biomarkers (PF1 + 2, TAT, PAP, PAI-1, TFPI, FVIII, FXIII).Metric: Correlation with Anti-Xa, VET, and TGA; exploratory path analyses of marker interrelations.Aggregation: Correlation coefficients with 95% CI; descriptive effect-size comparison.Time point: Parallel to VET and TGA sampling.Clinical relevance: Identifies mechanistic markers that may explain discordance between concentration-based assays (Anti-Xa) and functional assays (VET/TGA).3) Variable: Dose-exposure-response relationships (applied dose, Anti-Xa levels, VET, and TGA).Metric: Linear and nonlinear regression models linking administered anticoagulant dose to laboratory readouts.Aggregation: Regression coefficients (*β*) with 95% CI; model fit indices (*R*^2^, AIC).Time point: At all scheduled samplings, stratified by regimen type.Clinical relevance: Assesses whether dosing strategies achieve expected anticoagulant activity defined as Anti-Xa activity within the intended target range regarding dosage and whether functional assays reveal discrepancies not captured by Anti-Xa.4) Variable: Patient-level modifiers (e.g., sepsis status, SOFA score, renal function, albumin, BMI).Metric: Interaction terms in regression/mixed-effects models; subgroup analyses.Aggregation: *β* coefficients for interaction effects with 95% CI; stratified correlation estimates.Time point: As in primary outcome, stratified by clinical subgroup.Clinical relevance: Determines whether specific patient factors systematically influence anticoagulant effect or modify the correlation between Anti-Xa, VET, and TGA.5) Variable: Clinical complications (bleeding and thrombotic events within 24 h).Metric: Exploratory descriptive analysis of concordance between laboratory profiles and event occurrence; logistic regression if case numbers allow.Aggregation: Odds ratios with 95% CI (if feasible); otherwise descriptive frequencies.Time point: Event assessment in the 24 h prior to or following each sampling.Clinical relevance: Provides preliminary signal on the clinical predictive value of Anti-Xa, VET, and TGA in identifying patients at bleeding or thrombotic risk.

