### Handling for repeated measurements

2.14

All inferential analyses involving repeated measurements will apply mixed-effects modelling with patient-level random intercepts. Simple correlation coefficients are presented for descriptive purposes only.

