### Additional analyses

2.16

Dose–exposure–response relationships between administered anticoagulant dose, Anti-Xa activity, and VET parameters will be explored using linear mixed-effects models. Potential effect modification by patient-specific variables (e.g., age, sex, renal function, SOFA score, SAPS II) will be examined using interaction terms within the mixed-effects framework. No separate subgroup analyses are planned. Stratified analyses, if presented, will be considered descriptive. Exploratory analyses of clinical events (bleeding or thrombotic complications) will use logistic regression only if event numbers permit stable estimation. These analyses are considered hypothesis-generating.

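### Comparing the CT-RVV/Anti-Xa correlation across anticoagulation intensities can mix differences in Anti-Xa spread with differences in assay behaviour, and no slope-based comparison by intensity is specified

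*Protocol article*

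**What the plan says.** All references are to the protocol article.

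- Section 2.2 gives the purpose of sampling three intensity levels as "allowing comparisons of the correlation and adjustability of individualized anticoagulation across different degrees of anticoagulation intensity".
- Section 2.10, exploratory outcome 4, examines patient-level modifiers by interaction terms and subgroup analyses. It reports interaction coefficients together with "stratified correlation estimates". Its examples are sepsis, SOFA, renal function, albumin and BMI.
- Section 2.13.2 introduces its list with "Pre-specified modifiers include" and names sepsis, antithrombin, renal function and inflammatory markers. Section 2.16 gives age, sex, renal function, SOFA and SAPS II as examples. Neither names anticoagulation intensity. The primary model in Section 2.13.1 has a fixed effect for anticoagulant type only.
- On interpretation, the Introduction says that "weak or heterogeneous correlation would question whether VET-based monitoring offers advantages". The Abstract likewise ties the favourable conclusion to a correlation that holds across clinical states.
- On inference, Section 2.13.1 says: "Results will be reported as regression slope estimates (per 0.1 IU/mL increase in Anti-Xa activity) with 95% confidence intervals". Section 2.14 adds: "Simple correlation coefficients are presented for descriptive purposes only". Section 2.16 adds: "No separate subgroup analyses are planned. Stratified analyses, if presented, will be considered descriptive".

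**The concern.** A correlation coefficient is not a property of the assay alone. It combines the slope of CT on Anti-Xa, the scatter of CT about that line, and the spread of Anti-Xa in the patients who happen to be in the stratum. Intensity groups are formed on something closely tied to Anti-Xa, so their spreads may well differ from one another and from the pooled spread. A table of r by intensity could then look heterogeneous although CT responds to Anti-Xa in the same way throughout.

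This matters because the article words its conclusion in terms of correlation. It also treats prophylactic LMWH dosing, in the Discussion, as a setting where the usefulness of these assays is uncertain. A difference produced by spread could be taken as an answer to that question.

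**Working it through.** The article states no r by intensity, so there is no planned figure to reproduce. The check asks how far r can move when the assay behaves identically in every stratum.

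**Inputs from the article.** Planning correlations of 0.6 (UFH) and 0.669 (LMWH), Section 2.12. A cited systematic review that "reported low peak Anti-Xa levels ranging from 0.1 to 0.35 IU/mL", Introduction. 66 patients and about 1.54 effective observations per patient, Section 2.12.

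**Assumptions.** 0.6 and 0.669 are used as pooled correlations. The stratum SD ratios are assumed. So are the Anti-Xa ranges by intensity: the review's range is borrowed for prophylactic patients, and the other ranges are illustrative.

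**Step 1, formula.** Let CT = a + b × Anti-Xa + error, with the same b and residual SD everywhere. If a stratum's Anti-Xa SD is k times the pooled SD, its Pearson correlation is

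r_k = k·r / √(k²r² + 1 − r²).

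With r = 0.6, r² = 0.36 and 1 − r² = 0.64:

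- k = 0.6: √(0.1296 / 0.7696) = 0.41
- k = 0.5: √(0.0900 / 0.7300) = 0.35
- k = 0.4: √(0.0576 / 0.6976) = 0.29
- k = 0.3: √(0.0324 / 0.6724) = 0.22

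With r = 0.669, k = 0.75, 0.50 and 0.25 give 0.56, 0.41 and 0.22.

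**Step 2, Spearman version.** The formula is for Pearson r and the plan reports Spearman, so I simulated three equal strata with Anti-Xa uniform on 0.1–0.35, 0.3–0.6 and 0.5–1.1 IU/mL, a common slope scaled to 1 and a common residual SD.

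| Pooled Pearson r | Prophylactic | Intermediate | Therapeutic | Slope in each |
|---|---|---|---|---|
| 0.60 | 0.20 | 0.23 | 0.44 | 1.00 |
| 0.669 | 0.24 | 0.28 | 0.51 | 1.00 (prophylactic 1.01) |

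The stratum entries are Spearman r. The rank correlation varies about twofold while the slope does not change beyond simulation error.

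**Step 3, does the direction hold?** It does not hold in general.

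- With the residual SD of the 0.60 case, a wide prophylactic range (0–0.5) and a narrow therapeutic range (0.3–0.7) give 0.37 and 0.31, so the order reverses.
- With residual scatter proportional to level (30%) and the ranges of Step 2, Spearman r is 0.73 prophylactic and 0.58 therapeutic.
- With the same relative Anti-Xa spread in each stratum and proportional scatter, r is 0.69 throughout.

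**Step 4, precision.** If the 66 patients split equally, each stratum has 22, or 22 × 1.54 = 33.9 effective observations. The Fisher-z interval is tanh(atanh r ± 1.96/√(33.9 − 3)). For r = 0.2 it runs from −0.15 to 0.50, and for r = 0.6 from 0.33 to 0.78. Chance variation in stratum r is therefore large as well.

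**The case against.** The strongest reply is that nothing confirmatory rests on this comparison. The primary inference is a mixed-model slope, simple correlations and stratified results are declared descriptive, and listed modifiers are examined by interaction terms, with stratified correlations only beside them. Section 2.2 can be read as a reason for enrolling all intensities; Section 2.13.1 asks for Spearman coefficients only overall and by anticoagulant type. All of this stands, and it limits the point to a descriptive comparison and how it will be read.

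A reader might infer three stronger things that the documents do not support.

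- That r must fall in prophylactic patients. Intensity groups differ by definition in target level, not in spread. The article stresses wide variability at standard doses, gives no range by intensity, and Step 3 shows the order can reverse.
- That a stratified r is the only route planned for intensity. Exploratory outcome 3 in Section 2.10 fits dose, Anti-Xa, VET and TGA regressions by regimen type. That term is undefined and may cover intensity. These models link administered dose to the readouts, however, and do not specify the CT-Anti-Xa slope by intensity.
- That a low r within a narrow range is pure artefact. If CT cannot rank patients within the prophylactic range, that is a real limit on bedside use there. It does not show that the assay responds differently.

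Section 2.13 also refers to an analysis plan that is not shown, and the summary of a descriptive contrast could be settled there. That is fair for the detail. The announced comparison, the modifier lists and the interpretive sentence are in the article itself and do not fit together.

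**Conclusion.** The point holds as a weakness in an exploratory comparison and its interpretation; the primary slope analysis is untouched. With a common slope and constant residual SD, a pooled r of 0.6 can appear as 0.41 down to 0.22 in strata with 60% to 30% of the pooled Anti-Xa SD. Those ratios are assumptions, and the direction across intensities cannot be predicted from the article. What is firm is that differences in r between strata do not by themselves separate a changed CT-Anti-Xa relation from a changed Anti-Xa spread, and that no slope-based comparison by intensity is specified to do so. It should be corrected, but it does not threaten the trial's main result.

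**What to change.** - In Section 2.13.2, add intensity (prophylactic, intermediate, therapeutic) as an exploratory modifier, with a main effect and an Anti-Xa × intensity interaction.
- Compare strata by slope and by residual SD of CT about the fitted line, each with its uncertainty.
- Report the Anti-Xa SD or range beside every stratified r.
- State in the Introduction and in Sections 2.2 and 2.10 that differences in r between strata are not by themselves evidence of different assay performance.

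Cost: a three-level factor adds two main-effect and two interaction parameters, four fixed effects in all, to an exploratory model of 66 patients. Intensity is closely related to Anti-Xa, so the stratum slopes will be imprecise and should be presented as such. Table 1 lists UFH and LMWH dosage but not the intended intensity, so the target would have to be recorded for each sample. No additional blood sampling or assay is needed.
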